### Data analysis

Interim analysis will be performed on the pilot cohort. Primary and secondary outcomes will be described using descriptive statistics including percentages for categorical variables and mean and SD or median and IQR for continuous variables. Groups will be compared such as using ANOVA for parametric, Mann-Whitney U for non-parametric and χ^2^ for categorical tests. All tests of significance will be two-tailed and a p value ≤0.05 will be considered statistically significant.

We will use machine learning algorithms such as deep-learning-based natural language processing (NLPs) to analyse free-text data to identify variables associated with LCINS including genomic data. UCLH has deployed information retrieval platforms with NLP capabilities such as CogStack^13^ and MedCAT.^14^ These models allow further adaptations for new datasets and tasks using annotated data. Data will be validated by manual annotation of at least 10% of participants.

Data may be analysed with Cox proportional hazards to determine the association of variables identified (such as exposures and presenting symptoms) with one-year and five-year survival as an outcome. We assume at least 100 outcome events are required to perform survival analysis involving 10 covariates. Given the high mortality associated with lung cancer, it is possible that this threshold will be met even within the pilot cohort. We will also review the possibility of extending follow-up of study participants if required.

Once variables to be collected have been finalised, we will review missingness of data including likely missingness mechanisms. If survival analysis is performed, where appropriate, multiple imputation based on chained equations will be used to impute missing values for predictor variables with more than 10% missingness. Sensitivity analyses including limiting analysis to complete cases only will be performed to assess the robustness of the results.

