### Secondary objectives

Describe lung cancer outcomes such as stage at diagnosis, treatment and survival.Quantitatively or qualitatively measure the association of modifiable and non-modifiable factors that may be associated with LCINS including environmental measures, blood tests and genomic data.

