### Ethics and dissemination

The study is compliant with the requirements of General Data Protection Regulation (GDPR) (2016/679) and the UK Data Protection Act (2018). All investigators and study site staff will comply with the requirements of the GDPR (2016/679) with regards to the collection, storage, processing and disclosure of personal information and will uphold the Act’s core principles. Samples will be processed, stored and disposed in accordance with all applicable legal and regulatory requirements, including the Human Tissue Act 2004 and any amendments thereafter, and the applicable HTA Codes of Practice Departmental SOPs will be followed to facilitate regulatory compliance.

Ethical approval has been obtained from the Health Research Authority (HRA) (24/YH/0147). Access to patient records without explicit consent, including deceased patient records, is legally supported by the CAG (24CAG0077) and HRA. Any amendments to the protocol will be submitted for further approval. An annual review will be submitted to the CAG. The study is sponsored by UCLH.

As this is predominantly an observational study using data that are routinely collected within EHR, there will be no changes to usual clinical care and serious adverse events are not expected. All patient representatives thought the risk of being involved in the study was minimal.

Confidentiality and GDPR principles will be strictly adhered to. Risks to confidentiality will be minimised by requesting a minimally required dataset and processing to remove personal IDs where possible. All researchers have a duty of confidentiality and appropriate training.

Data will be anonymised and analysed two years after the study start date and on study completion. Only aggregated, anonymised data will be published. Data will be disseminated to the scientific and academic community through presentations at national and international conferences and publications. Together with our patient representatives, we will share our results with the public and patients through patient-facing charities, through social media and on hospital websites. Access to study data by external investigators can be requested by contacting the UCLH Joint Research Office and study Principal Investigator.

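### The article's general descriptive rule covers survival without an exception for censoring; applied as written, it would bias five-year and median survival substantially and one-year survival modestly

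*Protocol article*

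**What the plan says.** Under Secondary objectives, the protocol article commits without condition to "Describe lung cancer outcomes such as stage at diagnosis, treatment and survival". The Data analysis section sets one descriptive approach for all primary and secondary outcomes: "Primary and secondary outcomes will be described using descriptive statistics including percentages for categorical variables and mean and SD or median and IQR". It continues: "Groups will be compared such as using ANOVA for parametric, Mann-Whitney U for non-parametric and χ^2^ for categorical tests". Survival is not excepted from either sentence.

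A later paragraph of the same section brings in time-to-event methods, but conditionally: "Data may be analysed with Cox proportional hazards to determine the association of variables identified", "with one-year and five-year survival as an outcome". The missing-data paragraph repeats the condition and covers predictors, not unknown survival status: "If survival analysis is performed, where appropriate, multiple imputation based on chained equations will be used to impute missing values for predictor variables".

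On timing, Ethics and dissemination states "Data will be anonymised and analysed two years after the study start date and on study completion". The section on recruitment and consent ends follow-up at death, withdrawal or a single date five years after activation at the lead hospital. Sample size gives 25 participants per year, retrospectively from January 2019 and prospectively to 2029. Extending follow-up is only to be considered if needed.

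**The concern.** Percentages, means, medians, ANOVA, Mann-Whitney U and chi-squared all assume that each patient's value is known. Survival does not meet that assumption here. Entry is spread over years and follow-up closes on one date, so patients who are alive with less than one or five years of follow-up are to be expected at both analyses. In a percentage, such a patient has no value for one-year or five-year survival, and the result depends on whether the patient is counted as a survivor, counted as a non-survivor or left out. In a mean or median, the survival time is cut at the analysis date. In a group comparison, groups diagnosed more recently have shorter observed times whatever their prognosis.

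The Cox model does not settle this. It may not be run, and its stated purpose is association, whereas the description of survival is owed in any case. The Introduction notes how little is known about outcomes in never-smokers with lung cancer, so readers are likely to use the survival figures.

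**Working it through.** The article gives no survival projection to reproduce, so the check is what the named summaries would return when the true survival is known.

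**Inputs from the article**
- Analyses at 2 years after the study start and at completion (5 years).
- 25 patients per year.
- One-year survival of 48% (Introduction), or 40% (60% dead at one year, in the recruitment and consent section). Both refer to lung cancer in general.

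**Assumptions**
- Activation in mid-2024, so the retrospective window is 5.5 years.
- Uniform accrual, and censoring only at the analysis date.
- S(t) = exp(−λ t^k), with k = 1 (constant hazard) or 0.6 (decreasing hazard).
- One-year survival of 70% as an additional better-prognosis case.

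**Formulas.** Let W be the accrual span up to the analysis and h the horizon.
- Unknowns counted as survivors: b = [∫₀ʰ S(t) dt + (W − h) S(h)] / W
- Unknowns kept in the denominator as non-survivors: d = S(h)(W − h)/W
- Unknown fraction: u = b − d
- Unknowns dropped: c = d/(1 − u)
- Median of observed times: the x that solves S(x)(1 − x/W) = 0.5

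**Main case: two-year analysis, S(1) = 0.48, k = 0.6.** W = 5.5 + 2 = 7.5 and λ = −ln 0.48 = 0.734.

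*Five years.* True S(5) = exp(−0.734 × 5^0.6) = 0.1455.
- Share with under 5 years of potential follow-up: 5/7.5 = 67%.
- b = (1.697 + 2.5 × 0.1455)/7.5 = 0.275
- d = 0.1455 × 2.5/7.5 = 0.0485
- u = 0.275 − 0.0485 = 0.226
- c = 0.0485/0.774 = 0.063
- Standard error if all 25 × 7.5 ≈ 188 patients were informative: √(0.1455 × 0.8545/188) = 0.026. The errors of +13, −8 and −10 points are about three to five times that.

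*One year.* True S(1) = 0.48.
- b = (0.643 + 6.5 × 0.48)/7.5 = 0.502
- d = 0.48 × 6.5/7.5 = 0.416
- c = 0.416/(1 − 0.086) = 0.455
- Standard error: √(0.48 × 0.52/188) = 0.036. Two of the three conventions lie within one standard error; the third is 6.4 points low.

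*Median.* True (ln 2/0.734)^(1/0.6) = 0.91 years. The observed-time median is 0.70 years.

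**Range at the two-year analysis**
- Alive and unscorable at five years: 14% to 38% of the cohort.
- Median understated by 13–16% (constant hazard) or 17–23% (decreasing hazard) at 40–48% one-year survival, and by 29–49% at 70%.

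**At completion** (W = 10.5), the main case gives 23.8%, 9.1% and 7.6% for five-year survival (b, c, d) against 14.5%.

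**Different cohort split.** A separate simulation used 100 retrospective plus 125 prospective patients, which matches the target of 225, with shape 0.7. At completion, true five-year survival of 10.4% appears as 22.3%, 5.6% or 4.6%: the same pattern. Across all scenarios of that simulation (shapes 1 and 0.7, both analyses), the average Kaplan-Meier estimate was within 0.5 points of the truth at both horizons.

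**A percentage that works.** Limiting the denominator to patients diagnosed at least h years before the analysis gives S(h) without bias. At the two-year analysis, the five-year figure then rests on 25 × 2.5 ≈ 62 patients (standard error √(0.1455 × 0.8545/62.5) = 4.5 points); at completion, on 25 × 5.5 ≈ 137 (3.0 points). Nobody diagnosed after activation has five years of follow-up by completion, so no prospective patient contributes.

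**The case against.** The strongest reply is that the article prescribes nothing wrong for survival. Both lists are illustrative and are keyed to categorical and continuous variables, and no sentence says that survival time will be averaged or tested by ANOVA. The survival paragraph names Cox regression and counts outcome events, which shows that the authors think in time-to-event terms, and a fitted Cox model can also yield survival curves. The article condenses a fuller protocol, and naming an estimator is often left to that document or to an analysis plan. A percentage among patients with enough potential follow-up is unbiased. The study is also a feasibility pilot.

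Much of this stands. A reader might infer that the plan commits to censoring-blind summaries and that the reported survival will therefore be wrong. The text does not support that: Kaplan-Meier is left open, and the restricted percentage would be valid. Nor does it follow that the whole survival description depends on how living patients are counted, because the one-year error is mostly small.

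What does not stand is that this is only an omission. The article states an approach for every secondary outcome and leaves survival inside it. It makes the alternative optional and aims it at association, and it does not state the restriction that would make a percentage valid.

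**Conclusion.** The point holds in conditional form: if the general descriptive sentence is applied to survival as written, living patients with short follow-up bias the result. The bias is upward when they are counted as survivors and downward when they are dropped or counted as non-survivors. It is large for five-year survival and the median, and modest at one year unless unknowns are scored as non-survivors.

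The sizes rest on uniform accrual, a mid-2024 activation and the assumed survival shapes. The article's one-year figures are for all lung cancer, and never-smokers may differ. The direction does not depend on these choices. Severity is minor to moderate, because survival is a secondary, descriptive outcome of a pilot and the text leaves room to do it properly.

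**What to change.** In Data analysis, take survival out of the general rule. Suggested wording:

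> Survival is excepted from these rules. It will be described by Kaplan-Meier estimates of the median and of one-year and five-year survival with 95% confidence intervals, from a stated time origin, with living patients censored at last known follow-up. Groups will be compared on survival by log-rank test or Cox model.

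Percentages and means or medians remain suitable for fully observed outcomes such as stage and treatment.

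The cost is one to three sentences and no new data, because the possible Cox model already needs the same dates. The visible downside is wide intervals at late time points. In the main case at the two-year analysis, only about 62.5 × 0.1455 ≈ 9 patients would be observed alive at five years.

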### Sample size

It is estimated that our local hospital sees 400 patients with lung cancer each year. Between 10% and 20% (40–80) of these patients will be never-smokers. We believe it is feasible to recruit 25 participants per year both retrospectively (from 1 January 2019 to 2024 inclusive) and prospectively (from study start date in 2024 to 2029 inclusive), with an overall recruitment target of 225 participants. This will allow us to review feasibility of data collection and planned statistical analysis. We will then seek funding to expand the study across multiple sites to ensure sufficient power for data analysis. We will aim to choose appropriate sites across the UK to ensure the representativeness of the cohort.

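### The 10% cut-off for imputation works variable by variable, ignores joint missingness, and leaves predictors at or below 10% with no stated method for the Cox model

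*Protocol article*

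**What the plan says.** All of the relevant text is in the Data analysis section of the protocol article, apart from the pilot size.

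- The Cox model is optional: "Data may be analysed with Cox proportional hazards".
- Its size requirement is stated: "We assume at least 100 outcome events are required to perform survival analysis involving 10 covariates". The section adds that the pilot cohort may possibly reach this number and that longer follow-up will be considered if needed.
- Imputation is conditional, beginning "If survival analysis is performed, where appropriate, multiple imputation", and is then limited by a threshold: "multiple imputation based on chained equations will be used to impute missing values for predictor variables with more than 10% missingness".
- Before that, once the variables are final, "we will review missingness of data including likely missingness mechanisms".
- Complete-case analysis appears only as a check: "Sensitivity analyses including limiting analysis to complete cases only will be performed to assess the robustness of the results".
- The Sample size section sets the pilot "with an overall recruitment target of 225 participants".

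The article does not say how predictors at or below 10% missingness are handled. It gives no expected missingness for any variable.

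**The concern.** A Cox model with several covariates needs every covariate for a record to be used. What matters is therefore the share of participants with at least one gap, and a threshold on each variable's own percentage does not control that share. The rule can give odd results. A single predictor at 11% would be imputed and cost no records. Ten predictors at 9% each would all fall outside the rule and, if left unfilled with independent gaps, would cost 1 − 0.91^10 = 61% of records.

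Three things are at stake:

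- **Events.** The plan sets its own minimum of 100 events for 10 covariates and regards reaching it in the pilot only as possible. Records dropped for small gaps would reduce the events that enter the model.
- **Bias.** Predictors come from routine records and free text, and the retrospective group includes deceased patients. If thin records go with emergency presentation or early death, dropping incomplete records selects on outcome. This is a plausible risk. The article gives no figures that show it.
- **The sensitivity analysis.** If no predictor exceeds 10%, the rule imputes nothing. Unless another method fills the gaps, the main analysis and the complete-case check would be the same analysis.

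**Working it through.** **Inputs from the article:** 10 covariates, at least 100 events and a 10% threshold (Data analysis); 225 participants (Sample size), used here only as a scale.

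**Assumptions, because the article gives no missingness figures:** all ten covariates are equally incomplete, at a fraction m at or below the threshold; the gaps are left unfilled; a record with any gap is dropped.

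**Step 1. The plan's own figure.** 100 events / 10 covariates = 10 events per covariate, so 10 × 10 = 100. It reproduces.

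**Step 2. Loss with independent gaps.** Share lost = 1 − (1 − m)^10. The events column also assumes that missingness is unrelated to death.

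| m per covariate | Share lost | Left of 225 | Left of 100 events | Events per covariate |
|---|---|---|---|---|
| 2% | 1 − 0.98^10 = 18.3% | 183.8 | 81.7 | 8.2 |
| 5% | 1 − 0.95^10 = 40.1% | 134.7 | 59.9 | 6.0 |
| 10% | 1 − 0.90^10 = 65.1% | 78.5 | 34.9 | 3.5 |

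**Step 3. Range when gaps are not independent, at 10% each.**

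- Full overlap (the same participants lack everything): loss = m = 10%.
- No overlap: loss = min(1, 10 × 0.10) = 100%.
- Positively correlated gaps, simulated from a Gaussian copula with 400,000 draws: 49.6%, 40.3% and 26.2% at latent correlations of 0.3, 0.5 and 0.8. At 5% each, the same correlations give 30.8%, 24.7% and 15.3%.

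**Step 4. Fewer affected covariates.** A covariate that is complete, or above 10% and so imputed, adds nothing to the loss. With five affected covariates at 10% and independent gaps, the loss is 1 − 0.90^5 = 41.0%. With ten at 1%, it is 1 − 0.99^10 = 9.6%.

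**Step 5. Events needed at the outset to keep 100,** under the assumptions of step 2: 100 / 0.95^10 = 167 at 5% each, and 100 / 0.90^10 = 287 at 10% each. The second figure exceeds the pilot's 225 participants.

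**Step 6. With all incomplete predictors imputed,** no record is lost for a missing predictor: 225 of 225 participants and 100 of 100 events stay in.

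**The case against.** The strongest reply is that the article never prescribes deletion. It is silent below the threshold, and naming complete cases only as a sensitivity analysis suggests that the main analysis was meant to be something else. The Cox model is optional, survival is a secondary objective, and imputation applies only where appropriate. Extraction is to be tried on 100 patients before the variables are fixed, and missingness is then to be reviewed, so joint loss could be seen before any model is fitted. A condensed article may also leave the handling of small gaps, and the contents of the imputation model, to a fuller document.

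Much of this stands. A reader might infer that every predictor at or below 10% will be handled by deletion. The text does not say so; deletion is only what a standard Cox fit does if nothing else is specified. A reader might also take 65% as the most that could be lost. It is not a maximum. It is the value for ten covariates at exactly 10% with independent gaps, within a range of 10% to 100%. Nor can the event counts in the table be combined with the bias argument: they hold only if missingness is unrelated to death, and the bias argument supposes that it is related. The article also does not say whether the 100 events are counted before or after exclusions.

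The reply does not remove the cut-off itself. The threshold is a rule that the article states, and a fuller plan that followed it literally would carry the weakness forward. The missingness review is useful, but nothing in the text says that it may override the threshold.

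**Conclusion.** The point holds in a limited form. The stated cut-off is poorly chosen because it ignores joint missingness and leaves predictors at or below 10% outside the only method named. If those gaps are left unfilled, the loss would be about 18%, 40% or 65% of records at 2%, 5% or 10% missing in each of ten covariates with independent gaps. Positive correlation between gaps, or fewer incomplete covariates, would make it smaller. Whether the real loss is trivial or serious cannot be told from the article.

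Confidence is moderate. The weakness affects an optional, secondary analysis and leaves the descriptive primary objectives untouched. It is worth correcting because the correction is easy and the event requirement leaves little evident slack.

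**What to change.** Remove the restriction to predictors above 10%. State that, where imputation is appropriate, all incomplete predictors in the Cox model are imputed jointly in one chained-equations procedure. Include the event indicator and the cumulative hazard (for example, the Nelson-Aalen estimate) in the imputation model. This is a recommendation for the new wording; its absence from a condensed article is not itself a fault. Keep the complete-case analysis as the sensitivity analysis already planned. At the least, say how predictors at or below 10% are handled.

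The cost is one sentence in the Data analysis section and slightly more analysis work, with no additional data.

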### Patient and public involvement

A clinical team caring for never-smokers with lung cancer identified suitable individuals to discuss this research. Four individuals agreed to take part in an online patient engagement meeting. They range in age from mid-30s to late-60s and represent different ethnic and socioeconomic groups. They have been diagnosed with lung cancer for different lengths of time and have different stages of disease. They were renumerated for their time and participation.

The research protocol was adapted following this discussion, including:

Research design including which factors should be collected from EHR.The recruitment process including how to increase awareness of the opt-out process.The consent process including the PIS and consent form; for example, the term ‘never-smokers’ was defined in all patient-facing information.

We also discussed ethical considerations including their views on reviewing confidential data without explicit consent, and risks and benefits of the study. All representatives agreed there were no concerns and our research protocol is completely acceptable.

Our patient representatives will continue to engage with this research and ensure that the process remains acceptable to patients. They will also be involved in the analysis and dissemination including interpreting results and identifying research themes, reviewing plain English summaries and advising on the impact of results on the public. As discussed with our patient representatives, ongoing involvement will be through at least two 30-minute one-to-one meetings each year with each patient via Teams, Zoom or phone and minimum twice-yearly emails. Patient representatives have also agreed to additional group meetings for more collaborative discussions.

